## Abstract

**Background:**

Pediatric obesity is a critical public health issue. Augmenting care in multidisciplinary pediatric obesity clinics with innovative evidence-based technology to improve weight status and health outcomes is needed.

**Objective:**

This study describes the design and methods of an open trial pilot study to examine a remote patient monitoring system (RPMS) for children aged 8-17 years who are receiving treatment in a multidisciplinary pediatric obesity clinic.

**Methods:**

Participants will include 45 youth with obesity and their parents. Families will receive standard care in the clinic and the RPMS for 3 months. The RPMS consists of a tablet, weight scale, and pedometer. The system provides daily educational content and involves the use of the pedometer and weekly weigh-ins. Children and parents will complete baseline, posttreatment (month 3), and follow-up assessments (month 6). The primary aim of the study is to examine feasibility and satisfaction with the RPMS and assess its initial effectiveness.

**Results:**

We hypothesize high feasibility and satisfaction, with rates over 75%. Furthermore, after RPMS treatment, children will exhibit improved weight status, health outcomes, dietary intake, physical activity, health-related quality of life, self-efficacy, and home-food environment compared to before treatment. These gains are expected to persist at follow-up.

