### Study Design

This study will utilize an open trial design to examine the initial feasibility and effectiveness of implementing an RPMS in a pediatric obesity clinic. Participating families will receive standard care and the RPMS. After providing consent and assent, children and parents will complete questionnaires and objective measures as part of the pretreatment assessment. After using the RPMS for 3 months, families will complete the posttreatment assessment during a regularly scheduled follow-up appointment with health care providers at the pediatric weight management clinic. After an additional 3 months, participating families will also complete a follow-up assessment, similar to the pre- and posttreatment assessments, during a regularly scheduled clinic visit.

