### Participants

The study will recruit 45 families with a child aged 8-17 years who attends an outpatient pediatric obesity clinic and has a weight status in the obese range (BMI equal to or above the 95th percentile for age and gender), and parents and children who are fluent in English. Exclusion criteria are the following: (1) the child or parent having a history of cognitive impairment (developmental delay or intellectual disability) reported by the parent, which would impact their ability to understand and complete questionnaires or interact with the RPMS; and (2) the child having a medical condition, reported by parents, which may prohibit wearing of the actigraph device (eg, pacemaker).

Potentially eligible participants will be recruited through the pediatric weight management outpatient multidisciplinary clinic. When families present for a scheduled appointment, providers will provide them information about the study and ask if they are interested in knowing more about it. A trained research team member will discuss the study in more detail and obtain child assent, parent permission, and parent consent to participate. The research assistant will then assist the child and parent with the completion of baseline questionnaires and assessments.

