### Statistical Analyses

To examine aim 1, descriptive statistics (including mean [SD] and percentage values) of engagement with the RPMS will be used to examine feasibility and satisfaction scores on the basis of child and parent reports completed during the posttreatment assessment. To examine aim 2—initial effectiveness of the RPMS—repeated-measures analysis of variance will be conducted to determine whether there are significant differences in outcomes over time. Two-sample *t* tests will be used to compare differences in outcomes from pre- to posttreatment, pretreatment to follow-up, and posttreatment to follow-up. If necessary (eg, outcome data are skewed), nonparametric tests will be used to compare pretreatment, posttreatment, and follow-up scores. Maximum likelihood techniques will be utilized for missing data to provide unbiased and accurate estimates of variables regardless of the pattern of missing data (ie, random or completely random). Statistical significance will be set at *P*<.05.

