## Results

The study received ethics approval from the institutional review board in January 2019. Recruitment and enrollment began in August 2019. As of April 2021, 42 youth and their caregivers were enrolled in the study; however, participants continue to receive the RPMS intervention, and posttreatment and follow-up assessments are underway. Future outcomes will be published in professional peer-reviewed health-related research journals and presented at national, regional, or state-level professional meetings and conferences. Preliminary findings will be used to inform the development of a future study that will include a randomized controlled trial containing a larger sample of families and a standard care control group, evaluation of a refined RPMS, and cost-effectiveness analyses.

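### Persistence of gains at month 6 is examined only with difference tests, written as two-sample, which cannot show that gains were kept and barely detect a partly retained gain

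*Protocol article*

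**What the plan says.** The abstract (Results) predicts improvement from before to after treatment in weight status, health outcomes, behaviour and questionnaire measures, and adds: "These gains are expected to persist at follow-up". Study Design has the same families assessed again at month 6: "After an additional 3 months, participating families will also complete a follow-up assessment".

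For effectiveness, Statistical Analyses plans that "repeated-measures analysis of variance will be conducted to determine whether there are significant differences in outcomes over time". It then says that two-sample t "tests will be used to compare differences in outcomes from pre- to posttreatment, pretreatment to follow-up, and posttreatment to follow-up", with nonparametric tests if the data are skewed. The threshold is given once: "Statistical significance will be set at" P<.05.

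The section does not say which of the three comparisons decides persistence, how much of the gain must remain, or how a non-significant posttreatment-to-follow-up result will be read. Participants gives the size: "The study will recruit 45 families with a child aged 8-17 years". No effect size, SD, between-visit correlation or dropout rate is stated.

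**The concern.** Persistence is a claim that little or nothing was lost between month 3 and month 6. A difference test can show that something was lost. When it fails to reject, it does not show that the gain was kept. With about 45 children, failure to reject is a likely result under partial relapse, and nothing in the text rules out taking it as support for the hypothesis.

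The pretreatment-to-follow-up comparison answers a better question, namely whether month 6 is still better than baseline. Its two-sample form discards the pairing, so it would often miss benefit that is really there. The plan is therefore weak in both directions: the month-3-to-month-6 test cannot confirm maintenance, and the baseline-to-month-6 test can scarcely confirm residual benefit.

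The article says the findings will inform a later randomized trial, and its Discussion doubts whether 3 months of treatment is long enough for lasting change. What can be said about durability therefore matters to the next design.

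**Working it through.** The plan has no figure of its own to reproduce, because N=45 is given without a power calculation.

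**Inputs from the article:** n = 45 children, each measured at three visits; significance level 0.05 (taken as two-sided).

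**Assumptions, not in the article:** a true month-3 gain of 0.5 SD of within-child change; half of it lost by month 6, so 0.25 SD lost and 0.25 SD retained; between-visit correlation ρ = 0.8 where the two-sample form is examined; complete follow-up.

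**1. Posttreatment to follow-up, paired test**
- Noncentrality = 0.25 × √45 = 1.68; critical value t(0.975, 44) = 2.015.
- Probability of a non-significant result from the noncentral t: 0.625, so the loss is missed about 62% of the time.
- With 36 children (20% dropout, assumed) it is missed 69% of the time.

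**2. Precision of that change**
- 95% CI half-width = 2.015/√45 = 0.30 SD.
- Observed loss of half the gain: 0.25 ± 0.30, or −0.05 to 0.55. This runs from no loss to loss of the whole 0.50 gain.
- Observed loss of zero: the interval still reaches 0.30/0.50 = 60% of the gain.

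**3. Pretreatment to follow-up, half the gain retained**
- Within-child test: the standardized change is again 0.25, so power = 1 − 0.625 = 0.375, about 38%.
- Two-sample test, ρ = 0.8, in units of the between-child SD:
  - The change is 0.25 × √(2 × (1 − 0.8)) = 0.158.
  - The standard error the test uses is √(2/45) = 0.211, so it needs a difference of about 1.987 × 0.211 = 0.419.
  - The true standard error of the mean change is √(2 × 0.2/45) = 0.094, so the two-sample formula overstates it by 1/√0.2 = 2.2 times.
  - Required excess: (0.419 − 0.158)/0.094 = 2.8 true standard errors, a tail probability of about 0.3%. Simulation, which lets the estimated SDs vary, gives 0.5% to 0.6%.

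**4. How far step 1 depends on the assumptions**

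If the gain is expressed in between-child SDs instead, the chance that a paired test misses loss of half the gain is:

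| Gain (between-child SD) | ρ = 0.5 | ρ = 0.7 | ρ = 0.9 |
|---|---|---|---|
| 0.3 | 83% | 75% | 41% |
| 0.5 | 63% | 44% | 4% |
| 0.8 | 25% | 8% | <1% |

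The two-sample test on the same correlated data misses loss of half of a 0.5 SD gain 87% to 99% of the time over ρ = 0.5 to 0.9.

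**5. Complete loss, for contrast (gain 0.5 SD of within-child change)**
- Paired test: noncentrality 0.5 × √45 = 3.35; missed about 9% of the time.
- A significant gain, a missed loss and a significant pretreatment-to-follow-up result occur together in about 1% of simulated trials.
- Two-sample test, ρ = 0.8: the loss is missed about 84% of the time. But the month-3 gain is itself significant in only about 16% of trials, and the pretreatment-to-follow-up test is almost never significant.

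**The case against.** The strongest reply is that the article nowhere says a non-significant posttreatment-to-follow-up test will count as maintenance. A reader might infer that it would, but that predicts a misreading; it is not a stated rule. This stands.

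Second, the gains are defined relative to before treatment, so the natural test of persistence is pretreatment to follow-up, and that comparison is already planned. This stands too, and the posttreatment-to-follow-up test is not the only analysis bearing on the hypothesis. It does not close the point, because the planned check is written in a form that would detect a half-retained gain in well under 1% of trials at ρ = 0.8. It also carries no estimate of how much remains.

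Third, a reader might infer that even complete loss would pass as maintenance. The figures do not support this. A paired test misses complete loss only about 9% of the time. With the two-sample test at ρ = 0.8, the gain would rarely have been declared in the first place.

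Fourth, two-sample may be a slip for paired. If so, the sensitivity problem shrinks, and with high correlation and a moderate gain it largely disappears (4% missed in step 4). The logical point about non-significance remains.

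Finally, the persistence statement appears only in the abstract and not under Study Aims, the Discussion already concedes a small sample, and an analysis plan not shown may settle how results are read. All of this limits the weight.

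**Conclusion.** The point holds in limited form. The persistence hypothesis is paired with difference tests alone, and the pairwise tests are specified in a form that ignores that the same children return. A non-significant posttreatment-to-follow-up result could not establish persistence: about 62% of paired tests would miss loss of half the gain, with a CI half-width of 0.30 SD. The pretreatment-to-follow-up comparison is the right check but badly insensitive as written, at about 0.5% detection against 38% within child.

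These figures rest on an assumed gain of 0.5 SD of within-child change, the second pair also on a correlation of 0.8, and all on 45 children followed to month 6. Other plausible values move the 62% widely, as the table shows. The documents do not support saying that the trial will claim maintenance regardless of the truth, or that complete loss would usually be overlooked in a way that yields such a claim. For a small single-arm pilot this is a minor point, worth correcting because the correction needs no further data.

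**What to change.** In Statistical Analyses, state that:

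- persistence is judged on the pretreatment-to-follow-up change, estimated within child (paired analysis or a contrast from the repeated-measures model), with its 95% CI;
- the posttreatment-to-follow-up change is reported from the same analysis with its 95% CI;
- a non-significant posttreatment-to-follow-up P value is not presented as maintenance, and retention is called inconclusive if the interval includes loss of most of the month-3 gain.

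The two-sample wording should be replaced for all three pairs of visits, with signed-rank tests or similar paired methods as the nonparametric option.

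The cost is two or three sentences and no new data. The downside is a less favourable statement when the interval is wide. Under the assumptions of step 2, retention would be called inconclusive even with no observed loss, so the pretreatment-to-follow-up estimate would carry the conclusion. The article reports that in April 2021 assessments were still under way, so on its own account the change could precede the final analysis.

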**Conclusions:**

This study is novel in that it is the first to design, implement, and examine an RPMS in a pediatric obesity clinic. If the RPMS is feasible, effective, and easily accessible, it may prove to be a practical, acceptable, and cost-effective weight management treatment for youth seeking treatment for severe obesity.

**Trial Registration:**

ClinicalTrials.gov NCT04029597; https://clinicaltrials.gov/ct2/show/NCT04029597

**International Registered Report Identifier (IRRID):**

DERR1-10.2196/29858

## Introduction

Pediatric obesity is a critical public health issue in the United States. Serious comorbid health conditions including type 2 diabetes, heart disease, stroke, and cancers are common [1]. Younger individuals with obesity burden the health care system [2]. Specifically, pediatric obesity accounts for health care costs of over US $14 billion annually in the United States [3]. Efficacious pediatric obesity interventions are necessary to mitigate long-term health consequences and reduce health costs.

Standard care in multidisciplinary pediatric obesity clinics decrease adiposity in approximately 50% of treated youth [4,5]. However, providing and maintaining consistent care can be challenging when working with underserved children and families [6,7]. In Mississippi, over 50% of the state is rural, more than 35% of the population is Black or African American, and almost one-third of children live in poverty [8]. Mississippi also has the highest rates of pediatric obesity in the United States [9]. There is a significant need for innovative evidence-based technology to improve health and weight status.

Telemedicine use has increased owing to high rates of computer ownership, tablets, and cellphones, as well as easier internet access [10]. Insurance companies and health care organizations use telemedicine to support chronic disease management by developing remote patient monitoring systems (RPMSs) [10]. RPMSs provide patients with hardware and software that medically monitor health outcomes, provide educational information, automatically analyze health data, and alert patients and care providers of concerns [10]. RPMS efficacy studies have demonstrated improved health status in adults with chronic health conditions [11], such as diabetes [12], congestive heart failure [13], and obesity [14]. Nonetheless, applications of RPMSs in pediatric populations are limited. Four published studies have examined the applications of RPMSs in youth, having particularly focused on those with sleep apnea [15], cardiovascular implants [16], cancer [17], and type 1 diabetes [18]. These studies demonstrated feasibility, effectiveness, and reduced health care costs in pediatric populations; however, RPMSs have not been integrated into pediatric obesity clinics.

The primary objective of this study is to describe the design and methods of an open trial to test an RPMS designed to provide supplemental care to youth receiving treatment in a pediatric weight management clinic in Mississippi.

## Methods

### Ethics Approval and Trial Registration

This study was approved by the institutional review board at the University of Mississippi Medical Center (protocol# 2017-0083) and is registered on ClinicalTrials.gov (protocol# NCT04029597).

### Study Aims

The primary objective of this open trial is to pilot test an RPMS designed to provide supplemental health care to youth who are receiving specialty medical care in a multidisciplinary pediatric obesity clinic. Specifically, we will assess initial feasibility and satisfaction and examine initial effectiveness of the RPMS for 3 months. We hypothesize high feasibility with the use of the RPMS and satisfaction rates over 75%, and after treatment children are expected to exhibit improved health outcomes compared to before treatment and their parents are expected to report improvements in their children’s health-related quality of life and home-food environment.

### Study Design

This study will utilize an open trial design to examine the initial feasibility and effectiveness of implementing an RPMS in a pediatric obesity clinic. Participating families will receive standard care and the RPMS. After providing consent and assent, children and parents will complete questionnaires and objective measures as part of the pretreatment assessment. After using the RPMS for 3 months, families will complete the posttreatment assessment during a regularly scheduled follow-up appointment with health care providers at the pediatric weight management clinic. After an additional 3 months, participating families will also complete a follow-up assessment, similar to the pre- and posttreatment assessments, during a regularly scheduled clinic visit.

### Study Setting

The study will be conducted at the University of Mississippi Medical Center (UMMC) Pediatric Weight Management Clinic, a multidisciplinary outpatient medical clinic designed to treat children with obesity and related medical comorbidities. The clinic providers include a pediatric nurse practitioner and pediatric dietician who see every patient, as well as a clinical psychologist and mental health specialists who assess and treat patients with suspected mental health concerns. The study is being conducted in partnership with the UMMC Center for Telehealth, who assisted with the development of the RPMS intervention materials and provides oversight regarding RPMS equipment and participants’ use and interaction with the RPMS.

### Participants

The study will recruit 45 families with a child aged 8-17 years who attends an outpatient pediatric obesity clinic and has a weight status in the obese range (BMI equal to or above the 95th percentile for age and gender), and parents and children who are fluent in English. Exclusion criteria are the following: (1) the child or parent having a history of cognitive impairment (developmental delay or intellectual disability) reported by the parent, which would impact their ability to understand and complete questionnaires or interact with the RPMS; and (2) the child having a medical condition, reported by parents, which may prohibit wearing of the actigraph device (eg, pacemaker).

Potentially eligible participants will be recruited through the pediatric weight management outpatient multidisciplinary clinic. When families present for a scheduled appointment, providers will provide them information about the study and ask if they are interested in knowing more about it. A trained research team member will discuss the study in more detail and obtain child assent, parent permission, and parent consent to participate. The research assistant will then assist the child and parent with the completion of baseline questionnaires and assessments.

### Remote Patient Monitoring

The RPMS was developed in collaboration with UMMC Center of Telehealth. Patients enrolled in this open trial of the RPMS will interact with the system on a daily basis and with UMMC Center for Telehealth nurse care coordinators and research and clinical staff on an as-needed basis. The RPMS consists of an electronic tablet, weight scale, and pedometer. Patients will be asked to wear the pedometer daily to track engagement in physical activity and weigh themselves weekly to track weight during the 3-month period. Educational information specific to pediatric obesity–related medical complications and healthy eating and engagement in physical activity will be presented daily through brief presentations and video clips. Educational material and information were developed on the basis of behavioral family weight management treatments for pediatric obesity [19,20] and the social cognitive theory [21]. Daily assessments, which will include questions regarding health status and health behaviors, will be self-reported by the patient through the software program on the electronic tablet. Responses and vital signs and symptoms will be monitored by nurse care coordinators. The program contains a care management platform software that allows for data trends to be developed and analyzed to identify at-risk patients requiring action, such as follow-up phone calls to patients from the nurse coordinator and nurse coordinator informing the research and clinical team about patient symptoms. Solutions discussed and provided by the nurse coordinator and clinical research team may consist of the following: personalized interventions, targeted education, health coaching, behavior modification, medication adherence, and content to motivate patients. All health sessions are designed for patient engagement by providing quality educational content and self-management skills. The UMMC Center for Telehealth RPMS is linked to patients’ electronic medical record (ie, Epic) to facilitate communication between the nurse care coordinators and the medical team at the pediatric obesity. In addition, if patients have questions or need to contact the medical team the nurse care coordinators can facilitate that process, but patients and families are also able to contact (via secure messages, call, etc) the medical team providers, consistent with standard clinic procedures.

### Data Collection and Measures

Children and parents will complete the following measures and assessments at pretreatment (baseline), posttreatment (month 3), and follow-up (month 6) unless otherwise specified.

#### Child-Completed Questionnaires and Assessments

##### Height and Weight

Height without shoes will be measured using a stadiometer. Weight will be measured using a certified digital scale with 1 layer of clothing on and without shoes. Measurements will be conducted by trained clinical staff or research personnel. Data will be used to calculate child BMI, BMI *z* scores, and BMI percentiles using age- and gender-specific norms.

